### Sample size {14}

A sample size power analysis was performed using G*Power 3.1.9.7 [36] to ensure the study’s feasibility within its constraints and the available population of individuals with mild intellectual disabilities (MID) who abuse substances. The calculation was based on the primary hypothesis, which posits that participants receiving the Beat the Kick intervention will show greater improvement in autonomous motivation compared to those in the control group. The analysis assumed a between-group design with four measurement points: pre-treatment (T1), post-treatment (T2), and follow-ups at 1 month (T3) and 6 months (T4). An effect size of *f* = 0.25 (medium effect), a power of 80%, and a significance level of 5% (two-sided) were used, with default settings for the correlation among repeated measures (0.5) and the non-sphericity correction (ε = 1, assuming sphericity).

The power analysis indicated that a sample of 82 participants is required to detect the expected effect with 80% power. Given the elevated risk of dropout among individuals with MID and co-occurring substance use—estimated at approximately 40% based on previous studies—the recruitment target was increased to 138 participants.

This adjusted target accounts for anticipated attrition and ensures that a sufficient number of participants will complete the study to maintain statistical power. Although recruiting 138 individuals from this population poses logistical challenges, it is considered feasible through targeted recruitment strategies, including partnerships with care providers and the use of established professional networks. This adjusted recruitment plan acknowledges the inherent risks of higher dropout rates but ensures the robustness of the study’s findings and feasibility within its framework.

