### Recruitment {15}

Participants will be selected from the caseloads of six organizations affiliated with the Academic Collaborative Center Living with an intellectual disability (AWVB) at Tranzo, Tilburg University. Eligible individuals with MID who are not currently receiving substance abuse treatment will be identified through a random selection process carried out by the principal researcher. From this pool, 138 people with MID meeting the inclusion and exclusion criteria will be pre-assigned to either the experimental or control group using a Zelen design. The randomization process will be conducted by the principal researcher in an independent capacity to ensure objectivity and minimize bias. The intervention will be delivered by behavioral specialists from the six participating healthcare organizations to ensure standardized implementation across all sites.

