## Assignment of interventions: allocation

### Sequence generation {16a}

The study uses a Zelen pre-randomization design. Participants are individually randomized 1:1 to Beat the Kick or care-as-usual (CAU) using a centralized, computer-generated sequence with permuted blocks of variable size, stratified by addiction type (alcohol vs. cannabis/other drugs) to maintain balance across strata. Randomization is not clustered; clients from the same team may be allocated to either arm.

To minimize provider contamination while preserving individual randomization, trainers are assigned exclusively to a single arm (intervention or CAU) and do not deliver care in the other arm during the trial. Trainer and site identifiers are recorded at allocation; trainer will be modeled as a random effect in mixed-effects analyses to account for provider-level clustering. Any unavoidable cross-coverage will be documented a priori and examined in sensitivity analyses.

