Potential confounders, such as living arrangements (e.g., 24-h supervised care, outpatient services, or home-based support) and prior substance use treatment exposure, will be incorporated as covariates. These factors are expected to influence engagement and outcomes by shaping daily routines, support systems, and environmental stability. Trainer effects, which may vary due to differences in style, experience, or engagement, will be modeled as a random effect to minimize potential bias. Additionally, to prevent carry-over effects, trainers will be exclusively assigned to the intervention group, ensuring that training specific to Beat the Kick does not unintentionally influence CAU.

The secondary objective is to evaluate the intervention’s effectiveness in reducing substance use among adults with MID. It is hypothesized that the experimental group will show a greater reduction in substance use levels compared to the CAU group at follow-up. LMMs for secondary outcomes will mirror the primary model, including addiction type as a fixed effect (with exploratory interactions), and will adjust for baseline substance use levels.

To accommodate the Zelen design’s pre-randomization process, analyses will carefully consider group allocation at the pre-randomization stage, ensuring that group comparisons accurately reflect the intervention’s true effect. Sensitivity analyses will assess the robustness of results, including tests with and without outliers. Missing data will be handled using full information maximum likelihood (FIML), a robust method that leverages all available data and is generally preferred regardless of the underlying missingness mechanism [47]. Although FIML does not eliminate all bias under not-missing-at-random (NMAR) conditions, it typically yields less biased results than listwise deletion. Conclusions drawn under NMAR will be interpreted with appropriate caution, and the plausibility of the missing at random (MAR) assumption will be evaluated in light of the observed data structure and auxiliary variables.

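### The 82/138 sample size assumes independent participants and inflates only for dropout, although the protocol models clustering by trainer

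*Protocol article*

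**What the plan says.** Sample size {14} describes a G*Power run. On the design it says "The analysis assumed a between-group design with four measurement points". The effect size is f = 0.25, with "a power of 80%, and a significance level of 5% (two-sided) were used", a correlation of 0.5 among repeated measures and ε = 1. The result is given as "The power analysis indicated that a sample of 82 participants is required to detect the expected effect with 80% power". An expected dropout of about 40% raises the target to 138, and the section says this leaves enough completers to preserve power. It mentions no ICC, caseload or design effect.

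Two other sections treat providers as a source of correlation. Sequence generation {16a} assigns each trainer to a single arm and says "trainer will be modeled as a random effect in mixed-effects analyses to account for provider-level clustering". Statistical methods {20a} says "Trainer effects, which may vary due to differences in style, experience, or engagement, will be modeled as a random effect to minimize potential bias". The two differ on one detail: {16a} speaks of trainers in either the intervention or the CAU arm, while {20a} places trainers in the intervention arm only.

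On who delivers the programme, Recruitment {15} says "The intervention will be delivered by behavioral specialists from the six participating healthcare organizations". Neither the number of trainers nor the number of clients per trainer is given.

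**The concern.** The sample size and the primary model describe different data structures. The calculation treats every participant as an independent unit. The model allows clients of one trainer to resemble each other. Because no trainer works in both arms, differences between trainers do not cancel in the group comparison; they add to the variance of the intervention-arm mean. The margin above 82 is already committed to dropout, so nothing in 138 is set aside for this.

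At stake is how a null result would be read. A reader would set it against a stated 80% power that leaves out a variance source the protocol itself expects.

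**Working it through.** **Inputs from the document.** f = 0.25 (for two equal groups, d = 2f = 0.5), two-sided 5%, four measurements, correlation 0.5, ε = 1, N = 82 analysed (41 per arm), dropout about 40%, target 138 (Sample size {14}); allocation 1:1 (Trial design {8}).

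**Inputs assumed.** Trainer ICC of 0.02, 0.05 or 0.10, and k = 6 or 12 trainers per clustered arm. Six corresponds to one per organization in Recruitment {15}. It is an inference and not a guaranteed minimum, because Trial design {8} says that intervention and CAU therapists work for different organizations.

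**Step 1: reproduce the printed figure.** For the between-factor test, λ = f²·N·4/(1 + 3·0.5).
- N = 82: λ = 0.0625 × 82 × 4/2.5 = 8.2, with df 1 and 80; power 0.808.
- N = 80: power 0.798.

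So 82 is the smallest even N that reaches 80%, with independent participants. The group-by-time interaction option at the same f needs only 24, so 82 comes from the between-factor test.

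**Step 2: dropout.** 82/0.60 = 136.7, rounded up to 137 and made even at 138. Conversely, 138 × 0.60 = 82.8 completers. The whole increase is used up by attrition.

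**Step 3: add trainer clustering to the same test.** The variance of the four-visit mean is (1 + 3·0.5)/4 = 0.625. In a clustered arm it is multiplied by 1 + (41/k − 1)·ICC. For k = 6 and ICC 0.05 this is 1 + (6.83 − 1)·0.05 = 1.292. With the intervention arm alone clustered, the average inflation is (1.292 + 1)/2 = 1.146, so λ = 8.2/1.146 = 7.16 and power is 75.3%. The Satterthwaite columns take k − 1 df for the clustered arm and 40 for the other.

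| ICC | 6 trainers, df 80 | 6 trainers, Satterthwaite | 12 trainers, df 80 | 12 trainers, Satterthwaite | 6 per arm, both arms, df 80 |
|---|---|---|---|---|---|
| 0.02 | 78.5% | 74.4% | 79.8% | 78.5% | 76.3% |
| 0.05 | 75.3% | 70.4% | 78.4% | 77.0% | 70.2% |
| 0.10 | 70.2% | 64.3% | 76.2% | 74.5% | 61.3% |

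The first four result columns cluster the intervention arm only. The unclustered value is 80.8%. With 18 intervention-arm trainers and ICC 0.01, power stays at 80.5% (df 80).

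These figures apply the ICC to the four-visit mean. If it refers to a single score and is constant over time, the share on the mean is ICC/0.625. The 75.3% for six trainers at ICC 0.05 then becomes 72.2%.

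**Step 4: is this the primary test?** It is not. Outcomes {12} defines the primary endpoint as the T1-to-T2 change, and {20a} names group × time as the effect of interest. With d = 0.5 at T2, correlation 0.5, 41 per arm and no clustering:
- change score, variance 2(1 − 0.5) = 1: power about 61%;
- T2 adjusted for baseline, variance 1 − 0.5² = 0.75: power about 73%.

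The choice of contrast therefore moves power by about 7 to 20 points before trainers enter.

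**The case against.** The strongest objections concern scope and size.

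- **The arithmetic is correct as printed.** 82 and 138 both follow from the stated inputs, and randomization is individual. This stands: the fault is an omitted planning assumption, not a miscalculation.
- **The size rests on assumptions.** The document does not say that a trainer sees several clients, nor how many trainers there are. With 12 trainers and ICC up to 0.05 the loss is only about 1 to 4 points, small beside a conventional f = 0.25 and an approximate 40% dropout. This stands for size but not for direction.
- **Only a downward factor is counted.** Baseline and prognostic covariates, and partial data from dropouts under maximum likelihood, could raise power. That is true, but Sample size {14} does not rely on them, and they are a reason to compute power under the planned model.
- **A condensed article may leave trainer numbers and an ICC to a fuller document.** That is fair for the details. It does not cover the positive statement that the dropout allowance preserves power.

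A reader might infer that the stated 80% is too high for every contrast once trainers differ. The document does not support that. By the Step 3 formula with df 80, a baseline-adjusted mean of T2–T4 has about 93% power unclustered. With six intervention-arm trainers it has 92%, 90% and 86% at ICC 0.02, 0.05 and 0.10. Nor should a clustered figure for the four-visit main effect be printed as the trial's power. That test includes T1, before any trainer can have had an effect, and it is not the primary contrast.

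**Conclusion.** The point holds in a limited form. The 80% belongs to a test that assumes independence, the step to 138 reserves nothing for clustering, and the protocol's own model includes a trainer effect nested within arm. On the test used, any positive trainer ICC with more than one client per trainer puts power below 80.8%.

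The amount cannot be fixed from the document. It is a few points at most with 12 intervention-arm trainers and ICC up to 0.05. It becomes material with about six trainers at ICC 0.05 or above, with ICC near 0.10, or if both arms are clustered. All of this assumes 41 completers per arm and the ICCs and trainer numbers in the table. It does not show that the trial is underpowered for every contrast, and it supplies no single replacement for 80%.

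**What to change.** Keep N = 138 and amend the text:

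1. In Sample size {14}, state the planned number of trainers and clients per trainer.
2. Replace the single 80% with power at trainer ICC 0, 0.02, 0.05 and 0.10. Compute it for the primary T2–T1 group × time contrast under the planned model (baseline adjustment, trainer random effect), not for the four-visit main effect.
3. Delete the statement that inflating for dropout alone maintains power.
4. Reconcile {16a} and {20a} on whether CAU has trainers, since this decides whether one arm or both are clustered.
5. Spread intervention clients evenly over the trainers already trained. Using more of them helps: at ICC 0.05, going from six to 12 raises power on the sizing test from 75.3% to 78.4%, more than half of the 5.5-point loss.

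The cost is a short recalculation and some rewording, with no extra participants or staff. The stated power may become less favourable.

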### Trial design {8}

This multicenter, parallel-group superiority randomized controlled trial employs a Zelen design to evaluate the effectiveness of the Beat the Kick intervention in enhancing autonomous motivation and reducing substance use among adults with MID. The Zelen design ensures unbiased group assignment by randomizing 138 consecutive participants into two groups—treatment and CAU—prior to obtaining informed consent, thereby minimizing selection bias and mirroring real-world clinical scenarios [23]. Participants are allocated in a 1:1 ratio, with 69 individuals in each group.

Randomization occurs at the individual level, which introduces the potential risk of carry-over effects if therapists treat participants in both the CAU and Beat the Kick intervention groups. To mitigate this risk, therapists are exclusively assigned to either the intervention or CAU group, ensuring no overlap in their caseloads. Additionally, therapists from the intervention and CAU groups are employed by different organizations and do not collaborate or exchange information during the study period. This separation prevents contamination and enhances the validity of the findings. Following the study, therapists can provide valuable reflections on their experiences with the training, including its perceived effectiveness and practical applicability, offering further contextualization of the outcomes.

Assessments are conducted at four time points: pre-treatment (T1), post-treatment (T2), and follow-up evaluations at 1 month (T3) and 6 months (T4) after the intervention. This schedule allows for the measurement of both immediate and sustained effects of the intervention.

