### Who will obtain informed consent? {26a}

Recruitment will be conducted jointly by researchers from Tilburg University and care professionals at the participating organizations: care professionals identify and pre-screen eligible clients and introduce the study; Tilburg University researchers then confirm eligibility, provide standardized information in accessible formats, and obtain written informed consent. Researchers from Tilburg University with expertise in intellectual disabilities and substance abuse will be responsible for obtaining informed consent. They will ensure that all participants, or their legal representatives where applicable, fully understand the nature of the study, the intervention, and any potential risks or benefits. This process will be guided by the Zelen design, which facilitates ethical and transparent participant engagement.

Participants randomized to the intervention group (Beat the Kick) will be approached after randomization. Researchers will provide a detailed explanation of the intervention and study procedures, seeking their consent to participate in both the intervention and the study assessments, such as questionnaires and interviews. Participants randomized to the CAU group will be informed of their allocation and asked to consent to participate in the study assessments only, which are essential for evaluating study outcomes but do not involve active participation in the intervention. The primary goal is to seek consent directly from participants whenever possible. In cases where a legal representative is required, formal consent will also be obtained from the representative, in compliance with Dutch law and ethical guidelines. Consent from both the participant and their representative will be required, as the participant’s engagement is crucial for a motivation-based intervention. Researchers will use tailored communication strategies, including clear language and visual aids, to address any questions or concerns and ensure participants’ comprehension of the study details.

All questionnaires will be completed digitally or on paper, with assistance from the researcher if needed, ensuring accessibility and efficiency in data collection. Model versions of the participant information sheet and consent form for both study groups are provided as supplementary materials (Additional files 1 and 2).

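### The target of 138 is counted before consent but inflated for dropout only, so it leaves no room for refusals after randomisation

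*Protocol article*

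**What the plan says.** All references are to the protocol article.

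- **Sample size {14}.** The G*Power calculation is described thus: "The analysis assumed a between-group design with four measurement points". The effect size is f = 0.25, with "a power of 80%, and a significance level of 5% (two-sided) were used" and "default settings for the correlation among repeated measures (0.5) and the non-sphericity correction". It gives 82. The target is then raised to 138 for dropout of about 40%, and the section concludes: "This adjusted target accounts for anticipated attrition and ensures that a sufficient number of participants will complete the study to maintain statistical power".
- **Trial design {8}.** The Zelen design is said to work "by randomizing 138 consecutive participants into two groups—treatment and CAU—prior to obtaining informed consent", in a 1:1 ratio with 69 per arm.
- **Recruitment {15}.** "138 people with MID meeting the inclusion and exclusion criteria will be pre-assigned to either the experimental or control group using a Zelen design".
- **Abstract (Methods) and Who will obtain informed consent? {26a}.** Consent follows allocation in both arms. People allocated to Beat the Kick are approached by researchers "seeking their consent to participate in both the intervention and the study assessments". People allocated to care as usual (CAU) are asked to agree to assessments only.
- **Participant timeline {13}, Concealment mechanism {16b} and Implementation {16c}.** These give a different order. Enrolment follows screening and consent, and assignment comes after enrolment and the baseline assessments.

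The article states neither an expected rate of refusal after allocation nor a rule on replacing people who refuse.

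**The concern.** When people are randomised before they are asked, two losses occur in succession: some decline when approached, and some of those who agree later drop out. The inflation covers the second loss only. If 138 is the number randomised, as {8} and {15} say, those who decline are already inside the 138, and a person who declines all assessments contributes no data at any time point.

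Two things are at stake. The first is the power claim, which is worded as an assurance. The second is the intention-to-treat analysis. The note to Table 3 defines it as including everyone randomised, and the missing-data plan relies on maximum likelihood over available observations. A person with no observations adds nothing to that likelihood. Because low autonomous motivation is an entry criterion, willingness to consent could plausibly be related to the primary outcome.

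**Working it through.** **Inputs.** From {14}: f = 0.25, four measurements, correlation 0.5, ε = 1, two-sided 5%, 82 required, about 40% dropout, target 138. From {8}: 69 per arm, randomised before consent. The refusal rate q is not in the document, so 5% to 30% is assumed.

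**Step 1: reproduce 82.** For the between-group effect in a repeated-measures ANOVA, the non-centrality is λ = f² × N × m / (1 + (m − 1)ρ), with 1 and N − 2 degrees of freedom. Here λ = 0.0625 × N × 4 / 2.5 = 0.1 × N. N = 80 gives power 0.798 and N = 82 gives 0.808. So 82 is the smallest even total that reaches 80%, and the plan's figure is reproduced.

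**Step 2: reproduce 138.** 82 / (1 − 0.40) = 136.7, so 137, or 138 for equal arms. Dropout uses the whole margin: 138 × 0.60 = 82.8 expected completers, a surplus of 0.8.

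**Step 3: count refusals.** Expected completers = (138 − refusals) × 0.60, with power from the formula in step 1 at that expected number.

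| Refusals | Expected completers | Power |
|---|---|---|
| 0 | 82.8 | 81.1% |
| 1 | 82.2 | 80.9% |
| 2 | 81.6 | 80.6% |
| 3 | 81.0 | 80.3% |
| 4 | 80.4 | 79.97% |
| 10 | 76.8 | 78.1% |

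The count of 82 is missed at two refusals. Power of 80% is missed at four, which is 4/138 = 2.9%.

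**Step 4: assumed refusal rates, equal in both arms.** Expected completers = 138 × (1 − q) × 0.60. The last column is the number that would have to be randomised to keep 82 expected completers, 82 / 0.60 / (1 − q), rounded up.

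| q (assumed) | Expected completers | Power | Randomised to keep 82 |
|---|---|---|---|
| 5% | 78.7 | 79.1% | 144 |
| 10% | 74.5 | 76.8% | 152 |
| 20% | 66.2 | 71.7% | 171 |
| 30% | 58.0 | 65.8% | 196 |

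**Step 5: refusal in the Beat the Kick arm only, as an illustration.** Expected completers = (69 × (1 − q) + 69) × 0.60. At q = 10% this is 78.7 (power 79.1%) and at q = 20% it is 74.5 (76.8%). The power figures treat the arms as equal in size, which is an approximation.

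**Step 6: the order of events.** The abstract, {8}, {15} and {26a} put allocation before consent. {13}, {16b} and {16c} put consent or enrolment, and in the last two also baseline, before assignment. Under the first order 138 includes refusers. Under the second it could be a count of people who have already consented, and the shortfall would not arise. Both cannot hold.

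**The case against.** The strongest reply is that 138 may count consented people. {14} calls it a recruitment target, the abstract speaks of recruiting 138 adults, and {13}, {16b} and {16c} describe consent or enrolment before assignment. This stands as far as it goes: the document contradicts itself, and the shortfall exists only under the Zelen order. But that is the order the article names as its design, and {8} and {15} attach 138 to it explicitly.

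A reader might infer three stronger things that the document does not support.

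- *That 80% power is lost after two refusals.* It is not. Two refusals cross the count of 82, while power remains 80.6%. The thresholds are also sensitive to the approximate 40%. At 38% dropout, 138 absorbs five refusals before expected completers fall below 82 (133 × 0.62 = 82.5; 132 × 0.62 = 81.8). At 35% it absorbs eleven (127 × 0.65 = 82.6; 126 × 0.65 = 81.9).
- *That refusers are not replaced.* The article is silent. Replacement would sit badly with 138 as a fixed number randomised, but participant codes run to 200 in the data management section, which leaves room for more.
- *That the loss falls mainly on the Beat the Kick arm.* The joint consent request makes this plausible. No figure supports it, though, and people in CAU can refuse too. The text does not say that declining the programme bars someone from assessments, and the model consent forms are not shown.

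It is also fair to say that completers to study end are not the information available for the primary endpoint. That endpoint is the T2 − T1 change, and people lost after T2 still contribute to it. The power figures here belong to the plan's own four-measurement between-group calculation, not to that contrast.

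**Conclusion.** The point holds in a limited form. The arithmetic from 82 to 138 is right, but it allows for dropout only, while the stated design randomises 138 before consent. The surplus is 0.8 of an expected completer, so the assurance of enough completers is not a property of that design. At two refusals expected completers fall below 82, and at four refusals power falls below 80%. The early loss is small, about 0.3 percentage points per refusal. It becomes material at assumed refusal of 10% to 20%, where power is about 77% to 72%.

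This rests on the Zelen order being the one followed, on 40% dropout among those who consent, on refusers giving no data and not being replaced, and on refusal rates that are assumed. A larger loss in the Beat the Kick arm is a plausible risk, not a quantified fact.

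**What to change.** 1. Reconcile the abstract, {8}, {15} and {26a} with {13}, {16b} and {16c} on the order of consent, baseline and allocation. State whether 138 counts randomised or consented people, and whether refusers are replaced.
2. If 138 counts randomised people, restate {14} as expected completers = 138 × (1 − refusal) × 0.60, with the matching power over a stated refusal range, and remove the wording that the target ensures enough completers.
3. In the abstract and {26a}, make consent to assessments and consent to the programme separate items in the Beat the Kick arm. People who decline the programme can then stay in the T1–T4 assessments and be analysed as allocated.
4. Report refusals after allocation by arm.

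The cost is a less favourable power statement and an ethics amendment to one arm's consent form. No extra participants are needed for these changes, but they do not restore the power lost to refusal. Keeping 82 expected completers would instead mean randomising the larger numbers in step 4 of the working, against a projected pool of about 120 eligible clients a year across the six sites.
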